## Abstract

**Background:**

Approximately 90% of the 253 million blind or visually impaired people worldwide live in low- and middle-income countries. Lack of access to eye care is why most people remain or become blind. The World Health Organization Regional Office for Africa (WHO-AFRO) recently launched a primary eye care (PEC) package for sub-Saharan Africa—the WHO-AFRO PEC package—for integration into the health system at the primary health care (PHC) level. This has the potential to increase access to eye care, but feasibility studies are needed to determine the extent to which the health system has the capacity to deliver the package in PHC facilities.

**Objective:**

Our objective is to assess the technical feasibility of integrating the WHO-AFRO PEC package in PHC facilities in Nigeria.

**Methods:**

This study has several components, which include (1) a literature review of PEC in sub-Saharan Africa, (2) a Delphi exercise to reach consensus among experts regarding the technical complexity of the WHO-AFRO PEC package and the capacities needed to deliver it in PHC facilities, (3) development of PEC technical capacity assessment tools, and (4) data collection, including facility surveys and semistructured interviews with PHC staff and their supervisors and village health workers to determine the capacities available to deliver PEC in PHC facilities. Analysis will identify opportunities and the capacity gaps that need to be addressed to deliver PEC.

**Results:**

Consensus was reached among experts regarding the technical complexity of the WHO-AFRO PEC package and the capacities needed to deliver it as part of PHC. Quantitative tools (ie, structured questionnaires, in-depth interviews, and observation checklists) and topic guides based on agreed-upon technical capacities have been developed and relevant stakeholders have been identified. Surveys in 48 PHC facilities and interviews with health professionals and supervisors have been undertaken. Capacity gaps are being analyzed.

**Conclusions:**

This study will determine the capacity of PHC centers to deliver the WHO-AFRO PEC package as an integral part of the health system in Nigeria, with identification of capacity gaps. Although capacity assessments have to be context specific, the tools and findings will assist policy makers and health planners in Nigeria and similar settings, who are considering implementing the package, in making informed choices.

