Feasibility is a complex construct [25], which has been defined in different ways. For example, Snowden et al define feasibility as encompassing the following domains: political, cultural, or community acceptability as well as technical, cost, and legal feasibility [26]. This study focuses on technical feasibility, which comprises the technical complexity of an intervention and the technical capacities needed to deliver it [27]. To our knowledge, no technical feasibility study in relation to PEC in sub-Saharan Africa has been undertaken. Identifying the challenges, opportunities, and gaps in the technical capacities required will provide information for policy makers to make informed decisions about how the health system needs to be strengthened to deliver PEC as an integral component of PHC. The research is timely, as PHC reforms are currently underway in Nigeria, which include national policies to train primary-level staff and to provide essential drugs and consumables under the umbrella of Universal Health Coverage. These initiatives provide real opportunities to integrate PEC into PHC [24]. The overarching aim of this study is to determine the technical feasibility of implementing the WHO-AFRO PEC package into PHC facilities in Nigeria; in this paper, we describe, in detail, the methods to achieve this.

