##### Study Area

Nigeria has 36 states in six geopolitical zones. Enugu State was selected for the pilot study and Anambra State for the main study, both of which are in the southeast zone (see Figure 4 [34]).

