##### Selection of Districts, Facilities, and Participants

As this was a descriptive study, a sample of 48 facilities was estimated for a baseline study to be sufficient to determine a prevalence of 50% of PHCs with the technical capacity to implement PEC, with a margin of error of 20% with a 95% confidence level, a cluster design effect of 1.8, and accounting for a 10% nonresponse rate [37].

Facilities for inclusion in the main study in Anambra State, which has 21 districts with 235 PHC centers and 112 health posts (ie, a ratio of 2:1), were selected using a two-stage process. First, a list of districts was drawn up, stratified by rural, semiurban, and urban location, to create a sampling frame. Six districts were selected by selecting the appropriate number within each stratum to represent their distribution (ie, three semiurban to two rural to one urban) using simple random sampling. Second, within each district a list of PHC facilities was obtained from the National Primary Health Care Development Agency. The number of facilities—PHC centers and health posts—within each stratum was selected by probability proportionate to size in each district and to represent the 2:1 distribution of health centers and health posts.

The principal researcher administered the head-of-facility questionnaires and facility observational checklists; trained research assistants administered the CHEW and VHW questionnaires and the health promotion observational checklists. Paper forms were used to collect the data.

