## Discussion

This is the first study, to our knowledge, to assess the technical feasibility of integrating eye care into PHC in sub-Saharan Africa and the extent to which the health system needs to be strengthened to deliver it. An alternative approach to facilitate implementation in low-capacity settings would be to adapt the PEC package. There has been renewed interest in assessing the integration of services into health systems in LMICs [40], and the results from this study will be central to enabling policy makers to make an informed choice about what needs to be done to implement PEC in Nigeria.

The development of a conceptual framework for assessing health system interventions is important [41]. This study builds upon the technical complexity framework of Gericke to incorporate technical capacity assessments and will report a gap analysis in the system based on the WHO health systems framework. It is critical that countries implementing or scaling up new interventions have access to reliable, accurate, and comprehensive data on capacities and gaps in the system to deliver an equitable [42] and sustainable intervention. This study provides tools that could be adapted or modified for use in other countries in the region that plan to deliver the WHO-AFRO PEC package.

A limitation of the study is that it only addresses technical feasibility; other aspects of feasibility as delineated by Snowden, such as cultural, legal, financial, and political feasibility, may also need to be addressed. In addition, the assessment tools are cadre specific and designed for the Nigerian PHC context and may not be applicable to other settings. In this study, the sample size was 48 facilities. The study may not have been powered sufficiently to assess any capacity differences between health centers and health posts.

Results of the study will be disseminated to stakeholders in PHC and eye care in Nigeria by communique at stakeholders’ meetings and at local, national, and international ophthalmology and public health conferences, as well as in peer-reviewed journals.

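### The stated objective, aim and conclusion are national, but available capacity is surveyed in one state only, and neither the abstract nor the limitations says so

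*Protocol article*

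**What the plan says.** The Protocol article sets a national target in three places.

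- Abstract, Objective: to "assess the technical feasibility of integrating the WHO-AFRO PEC package in PHC facilities in Nigeria".
- Introduction, final paragraph (overarching aim): to "determine the technical feasibility of implementing the WHO-AFRO PEC package into PHC facilities in Nigeria".
- Abstract, in its concluding paragraph: "This study will determine the capacity of PHC centers to deliver the WHO-AFRO PEC package as an integral part of the health system in Nigeria".

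The Methods describe a much narrower survey. Study Area first gives the size of the country, "Nigeria has 36 states in six geopolitical zones", and then the choice of states: "Enugu State was selected for the pilot study and Anambra State for the main study, both of which are in the southeast zone". Selection of Districts, Facilities, and Participants gives the frame as "Anambra State, which has 21 districts with 235 PHC centers and 112 health posts". Six districts were drawn at random within location strata, and 48 facilities were taken from them.

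The Discussion opens its limitations with "A limitation of the study is that it only addresses technical feasibility". It adds that the tools may not transfer outside the Nigerian PHC setting, and that power may be too low to compare health centers with health posts. It does not mention that one state was surveyed.

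**The concern.** The study compares the capacity required to deliver the package with the capacity that facilities have. The second half of that comparison comes from the facility survey and the linked interviews, all in Anambra. A sample drawn within one state carries no information on how facilities in other states differ, so it cannot by itself support a statement about PHC facilities across Nigeria.

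The Discussion presents the results as central to informed choices about implementing primary eye care in Nigeria. A planner who reads only the abstract sees 48 facilities and a national conclusion, and nothing there signals a single state. Capacity gaps found in Anambra could then be taken as the gaps of states that were never surveyed.

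**Working it through.** **1. The plan's own sample size.** Inputs from Selection of Districts, Facilities, and Participants: prevalence p = 0.50, margin d = 0.20, 95% confidence (z = 1.96), design effect 1.8, nonresponse 10%.

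- Simple random sample: n = z² p(1 − p) / d² = 1.96² × 0.25 / 0.04 = 24.01
- With the design effect: 24.01 × 1.8 = 43.22
- With nonresponse: 43.22 / 0.9 = 48.02 (multiplying by 1.1 instead gives 47.54)

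The stated 48 reproduces. The 95% half-width is 1.96 × √(0.25 × 1.8 / n), which is 0.190 with 48 facilities and 0.201 with 43 (48 less 10%). The planned margin of 20 percentage points is met.

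**2. What that margin refers to.** The only clusters in the described selection are districts, so I take the design effect of 1.8 to cover clustering within districts. Nothing in the calculation represents variation between states, and with one state surveyed none could be estimated. The margin therefore describes facilities in Anambra.

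**3. Coverage.**

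| Level | Surveyed | Available | Share |
|---|---|---|---|
| Zones | 1 | 6 | 16.7% |
| States | 1 | 36 | 2.8% |
| Districts in Anambra | 6 | 21 | 28.6% |
| Facilities in Anambra | 48 | 235 + 112 = 347 | 13.8% |

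The random step starts at the third row. Inference from the design reaches the last two rows and stops there. The pilot does not widen it: it covered three facilities in one district of Enugu State, in the same zone, and served to test the instruments.

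**4. Which components are tied to Anambra.**

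- Literature review and Delphi exercise: the literature and the panel's experience relate to sub-Saharan Africa. They give the technical complexity and the capacities required, and are not tied to one state.
- Review of guidelines and policies: this addresses limitations in national documents, and is not tied to one state.
- Facility survey, CHEW and VHW questionnaires, checklists, and interviews with facility heads and district supervisors: all in the main study in Anambra. They give the capacity available.

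The quoted conclusion promises the capacity of PHC centers to deliver the package, which is what the last group measures.

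**5. What the limitations cover.** They name three things: the restriction to technical feasibility, transfer of the tools to other settings, and power by facility type. The second concerns settings outside the Nigerian PHC context and so treats Nigeria as one setting. None concerns how well one state represents the other 35.

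**The case against.** **The scope is disclosed.** The Methods name the state, give its zone, and carry a section heading for the main study in Anambra. A careful reader of the full article is not misled about where the data came from. This stands, and it limits the problem to the abstract, the aim, the conclusion and the limitations. It does not remove the mismatch there.

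**The reference to Nigeria may only name the setting.** In the conclusion it follows the words on the health system, and the next sentence allows that capacity assessments depend on context. The Introduction likewise asks for feasibility studies in every implementation setting. But the sentence that makes the allowance goes on to offer the findings, as well as the tools, to planners in Nigeria and similar settings. It does not say that one state was surveyed.

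**Parts of the study do reach beyond Anambra.** This is correct. Technical feasibility is defined as complexity plus the capacities needed, and both come from the literature review and the Delphi exercise. The analysis also separates limits in national policy from limits in delivery at district or facility level. Only the available-capacity part is bound to Anambra, and the fix should respect that.

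**Stronger readings that the document does not support.** A reader might infer that a national estimate with a confidence interval is planned and would miss its target. The data analysis section plans only frequency tables and simple descriptive analyses, with the facilities visited as the denominator in its example. A reader might also infer that the 50% prevalence behind the sample size is a national figure. It sits under the Anambra heading, directly before the Anambra frame, and needs no change. Nor can the distance between Anambra and the country be put in percentage points, because the document gives no between-state variation. Finally, the absence of a reason for choosing Anambra is not a fault in a condensed article, since that rationale may stand in the full protocol.

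**Conclusion.** The point holds as one about scope of inference. The objective, aim and conclusion claim capacity for PHC facilities in Nigeria, while the survey supports inference to one state of 36, in one zone of six. The abstract and the limitations leave this unsaid. This is a conclusion that goes beyond its sampling frame, not a detail left out for brevity.

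The sampling within Anambra and the sample size of 48 are sound for their stated inputs, and the survey remains valid for that state. The verdict rests on the described selection alone: random selection begins at district level within Anambra, and no other state contributes data to the main survey. It needs no assumption about how large the differences between states are. The article reports the survey as complete and the gap analysis as in progress, so the reporting can still be worded to match the frame.

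**What to change.** 1. In the abstract, the overarching aim and the conclusion, state that the available-capacity and gap findings apply to PHC facilities in Anambra State.
2. Keep statements beyond Anambra for the components not limited to it: the literature review and Delphi exercise on complexity and required capacities, and the review of national guidelines and policies.
3. Add to the limitations that the survey covered one state in one geopolitical zone, and that other states need their own capacity assessment, for which the tools are available.

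This changes wording only. No new data, sampling or calculation is needed. The downside is a narrower claim: the study would report capacity for Anambra alongside wider findings on what the package requires and what national policy provides for.

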**International Registered Report Identifier (IRRID):**

DERR1-10.2196/17263

## Introduction

Approximately 253 million people are blind or visually impaired worldwide, 90% of whom live in low- and middle-income countries (LMICs) [1]. In Nigeria, about 4.25 million adults are blind or visually impaired and over 80% of the blindness is due to avoidable causes [2,3]. Lack of access to eye care services is one of the reasons why people remain or become blind [4]. Cataracts are the most common cause of blindness in Nigeria [2], and high-quality cataract surgery should be accessible and affordable for all. However, in the Nigeria National Blindness and Visual Impairment Survey, almost half of all eyes that had undergone a procedure for cataract treatment had undergone couching—a traditional procedure to treat cataracts—often with poor visual outcomes. Glaucoma, which causes irreversible visual loss, was the second-most common cause of blindness [2]. Although early treatment can prevent or slow progression of the disease, in Nigeria people with glaucoma present very late to eye care services, often already blind in one or both eyes.

Other blinding-eye conditions in Nigeria include uncorrected refractive error [5], trachoma, and diabetic retinopathy. Presbyopia, the age-related decline in near vision, affects an estimated 20 million adults in Nigeria [6] and can lead to considerable productivity losses if uncorrected. Although blindness in children is rarer than in adults, many of the blinding conditions in LMICs, such as measles infection and vitamin A deficiency, can be prevented at the primary level [7,8].

Other eye conditions that cause ocular morbidity for which access to eye care is needed include dry, irritable eyes and allergic and infective conjunctivitis [9]. There is, therefore, a need for LMICs to provide universal access to eye care, not just for blinding conditions but also for conditions causing troublesome symptoms. Approximately 25% of Nigerians have ocular conditions [9]; with a population of 200 million, this means that approximately 50 million Nigerians are in need of eye care.

In LMICs, most eye care is delivered in secondary- and tertiary-level facilities, which are mainly located in urban areas. This leads to inequity in access, higher costs for patients and providers [10], and the patronage of other sources of care (eg, informal drugs sellers, traditional and spiritual healers, and couchers), which may exacerbate the visual loss through harmful practices or delayed access to appropriate treatment [9,11]. Over 35% of Nigerians with ocular problems consult an informal drug seller as a first option, primarily due to a lack of access to eye care services [9].

One way to improve access to eye care in LMICs is to integrate eye care into primary health care (PHC) [10], which is advocated by the World Health Organization (WHO) in their report Universal Eye Health: Global Action Plan 2014-2019 [12]. Primary eye care (PEC) entails the following elements: health protection, health promotion, specific preventive measures, detection and treatment of common eye conditions, detection and referral of more complex conditions, and record keeping. The health promotion elements can be delivered in the community as well as in facilities, while the other components principally take place in PHC facilities.

However, delivering PEC can have challenges; these include low PEC skill levels [13], inadequate supervision [14], and inadequate equipment and supplies [15]. A review of the literature on PEC in sub-Saharan Africa showed that there has been no consensus on the scope of PEC nor guidelines on the technical skills PHC workers require to implement eye care; this has resulted in deficient training and inadequate supervision [16]. To encourage uniformity of the scope of PEC in sub-Saharan Africa, the WHO Regional Office for Africa (WHO-AFRO) recently launched a package of evidence-based interventions for PEC: the WHO-AFRO PEC package [17]. The package can be subdivided into two broad elements: health promotion and facility-based eye care. The latter comprises five evidence-based algorithms and protocols on how to measure distance and near visual acuity, administer eye medication, remove foreign bodies, apply an eye patch, document findings, and refer and counsel patients. The purpose of the package is to strengthen the capacity of PHC workers in sub-Saharan Africa to manage patients with eye conditions [17] and widen access to eye care [18]. The package has been pilot-tested in Rwanda and Kenya [18].

In Nigeria, the health system has three tiers of service delivery—primary, secondary, and tertiary (see Figure 1, A)—staffed by appropriate cadres. The PHC system provides basic services and is often the first point of contact with the health system and the only source of health care for the majority of Nigerians in rural and remote communities [19]. PHC is delivered in health centers and smaller units called health posts. PHC staff comprise junior community health extension workers, community health extension workers (CHEWs), community health officers, and nurse midwives (see Figure 1, B).

**Figure 1 figure1:**
[figure not shown]
Human resources for health in Nigeria (A) across the tiers of the health system and (B) at primary health care (PHC) facilities. CHEW: community health extension worker; CHO: community health officer; JCHEW: junior community health extension worker; NMW: nurse midwife.

Challenges of delivering PHC in Nigeria include, but are not limited to, shortage of health workers and absenteeism [20], infrastructural decay and poor funding [21], a dearth of basic equipment [22], and lack of trust in the system by the community [23]. Attempts have been made by nongovernmental organizations to implement PEC in some parts of Nigeria by training a limited number of staff using their own curricula and providing basic equipment. However, these initiatives were only scaled up with financial support in one state, so they were not scalable nor sustainable [24]. Nevertheless, to deliver an effective and sustainable intervention, it is important that feasibility studies are conducted in each implementation setting. Feasibility research can help identify the opportunities and challenges in implementing a new health initiative, including PEC, which can only be as efficient as the PHC system into which it is built [16].

Feasibility is a complex construct [25], which has been defined in different ways. For example, Snowden et al define feasibility as encompassing the following domains: political, cultural, or community acceptability as well as technical, cost, and legal feasibility [26]. This study focuses on technical feasibility, which comprises the technical complexity of an intervention and the technical capacities needed to deliver it [27]. To our knowledge, no technical feasibility study in relation to PEC in sub-Saharan Africa has been undertaken. Identifying the challenges, opportunities, and gaps in the technical capacities required will provide information for policy makers to make informed decisions about how the health system needs to be strengthened to deliver PEC as an integral component of PHC. The research is timely, as PHC reforms are currently underway in Nigeria, which include national policies to train primary-level staff and to provide essential drugs and consumables under the umbrella of Universal Health Coverage. These initiatives provide real opportunities to integrate PEC into PHC [24]. The overarching aim of this study is to determine the technical feasibility of implementing the WHO-AFRO PEC package into PHC facilities in Nigeria; in this paper, we describe, in detail, the methods to achieve this.

